**1. Research content**

Study subjects: patients with Low anterior resection syndrome

Intervention: electroacupuncture

Effect indicators: improvement in Low anterior resection syndrome score

Study type: Randomized controlled trial

**2. Protocol**

**2.1 Participants**

2.1.1 Western diagnostic criteria

low anterior resection syndrome (LARS) is defined as a patient who has at least one of the following eight symptoms and causes at least one of the following eight consequences after total mesorectal excision or low anterior resection for rectal cancer: Eight symptoms (variable/unpredictable bowel function, intermittent bowel movements, increased bowel frequency, pain during repeated bowel movements, difficulty emptying, urgency to bowel movements, fecal incontinence, defecation) and eight consequences (toilet dependence, excessive concern with bowel function, dissatisfaction with bowel function, need to use coping strategies to manage bowel function, psychological and emotional health, social and daily activities, intimacy Relationships, influencing roles, commitments and responsibilities).

2.1.2 TCM syndrome diagnostic criteria

N/A

2.1.3 Inclusion criteria

① Age between 18 and 75 years of any gender;

② Diagnosis of LARS confirmed at least one month after rectal resection or stoma closure (LARS score ≥ 21).

③ Provide written informed consent.

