**2.3 Randomization and Blinding Procedures**

A stratified block randomization method will be employed, with stratification based on study centers. Eligible participants will be randomly assigned in a 1:1 ratio to either the electroacupuncture (EA) group or the sham acupuncture (SA) group. The randomization sequence will be generated using SAS software by an independent statistician who is not involved in any aspect of the trial. Randomization numbers will be managed and safeguarded by a designated randomization coordinator, who will not participate in the intervention, outcome assessment, or statistical analysis.

For each eligible participant enrolled, the screening personnel will obtain the corresponding randomization number by phone from the randomization coordinator. Throughout the trial, the randomization sequence will remain concealed from all other study personnel to ensure allocation concealment.

Blinding will not be applied to the acupuncturists due to the nature of the intervention. However, patients, outcome assessors, and statistical analysts will remain blinded to group allocation to minimize potential bias.

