**2.5 Outcome Measures**

**Primary outcome**

Change in LARS score from baseline at week 8.

The LARS score is a validated self-rating scale to assess bowel function after low rectal resection and consists of five items: fecal incontinence, urinary incontinence, bowel frequency, bowel aggregation, and urgency, with scores ranging from 0 to 42. The severity of bowel dysfunction can be categorized as: no LARS (0-20), mild LARS (21-29), or severe LARS (30-42).

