**2.8 Data Entry and Statistical Analysis**

A modified intention-to-treat (mITT) approach will be applied. All randomized participants who meet inclusion criteria will be included in the statistical analysis. Continuous variables will be expressed as mean ± standard deviation (M ± SD) or as median with interquartile range, depending on distribution. Categorical variables will be presented as frequencies, proportions, or percentages.

Baseline demographic and clinical characteristics will be compared using analysis of variance (ANOVA) or chi-square (χ²) tests. Between-group differences in outcomes will be analyzed using t-tests, rank-sum tests, ANOVA, or χ² tests, as appropriate. For repeated measures outcomes, repeated-measures ANOVA will be employed.

All statistical tests will be two-sided, with a significance level of α = 0.05. A p-value < 0.05 will be considered statistically significant. Statistical analyses will be conducted using SPSS software.

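### Section 2.8 names only unadjusted tests for the week-8 LARS comparison, so baseline score, centre and time since surgery go unused and some precision is given away

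*Protocol*

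**What the plan says.** Section 2.1.3 of the protocol, criterion 2, requires LARS (a score of 21 or more) to be confirmed "at least one month after rectal resection or stoma closure". It gives a lower bound only, and the exclusion criteria in 2.1.4 add no upper one.

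Section 2.3 describes the allocation: "A stratified block randomization method will be employed, with stratification based on study centers". No other stratum is named.

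Section 2.5 defines the primary outcome as "Change in LARS score from baseline at week 8", so a baseline LARS score must exist for every patient analysed.

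Section 2.8 gives the methods: "Between-group differences in outcomes will be analyzed using t-tests, rank-sum tests, ANOVA, or χ² tests, as appropriate". Repeated-measures ANOVA is added for repeated outcomes. No covariate is named for any analysis, and time since surgery or stoma closure appears nowhere as a stratum, covariate or subgroup.

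**The concern.** Three pieces of baseline information could sharpen the primary comparison, and section 2.8 uses none of them.

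- **Baseline LARS score** is subtracted to form the change but is not adjusted for. An ANCOVA estimates the slope on baseline from the data; a raw change score fixes it at one.
- **Centre** is the stratification factor. An analysis that ignores it does not match the design and leaves any between-centre variance in the error term.
- **Time since resection or stoma closure** can run from one month to any number of years. If the 8-week change depends on it, that variance also stays in the error term. The protocol does not expressly order the date to be recorded, but criterion 2 cannot be checked without it.

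At stake is the precision of the estimate, in a trial whose sample size leaves almost no spare power if the assumed 20% drop out. Validity is not at stake. Covariates chosen after the data are seen would be open to challenge, so they need to be named beforehand.

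**Working it through.** **Inputs**
- Section 2.2: expected falls of 6.8 and 4.1 points, so the difference is 6.8 − 4.1 = 2.7; SD 5; dropout 20%; total 136.
- Section 2.3: 1:1 allocation. Section 2.8: two-sided α = 0.05.
- Power is not stated. 80% is inferred because it reproduces 136.

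**The plan's own figure**

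n per arm = 2 × SD² × (1.960 + 0.842)² / difference² = 2 × 25 × 7.849 / 7.29 = 53.8, rounded up to 54.

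With dropout: 54 / 0.8 = 67.5, rounded up to 68 per arm, or 136 in total. The stated figure is reproduced. Two-sided 85% or 90% power would give 156 or 184, which do not match.

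**Power without covariates** (noncentral t)
- 54 per arm: SE = 5 × √(2/54) = 0.962; 2.7 / 0.962 = 2.81; 106 degrees of freedom; power 79.4% (80.1% by normal approximation).
- 68 per arm, if no outcome were missing: power 87.8%.

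**Power with time since surgery as a covariate**

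The documents give no R², so a range is assumed. Residual SD = 5 × √(1 − R²), with 54 per arm:

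| Assumed R² | Residual SD | Power |
|---|---|---|
| 0 | 5.00 | 79.4% |
| 0.02 | 4.95 | 80.2% |
| 0.05 | 4.87 | 81.4% |
| 0.10 | 4.74 | 83.4% |
| 0.20 | 4.47 | 87.5% |

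R² here should be read as the share of variance left after baseline score and centre. The table keeps 5 as the starting SD, as if those two explained nothing. Whatever they do explain would raise the starting power, and the documents do not allow that part to be computed.

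**Cost if the covariate is useless**

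One degree of freedom out of 106 leaves power at 79.4%. A covariate also differs between arms by chance, and estimating its slope inflates the variance of the treatment effect. For k normally distributed covariates and N patients the average factor is (N − 3)/(N − k − 3). With N = 108 and k = 1 this is 105/104 = 1.0096, the effective SD is 5 × √1.0096 = 5.02, and power is 79.0%. The worst case is therefore about 0.4 of a percentage point. Break-even is an R² of about 1/105, or 1%. With the same factor applied, R² of 0.02 and 0.10 give 79.8% and 83.1%, so the range is still about 80–83%.

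**Size of chance imbalance**

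The SD of the shift in the unadjusted estimate is 5 × √R² × √(2/54), which is 0.14, 0.22 and 0.30 points at R² = 0.02, 0.05 and 0.10, against a target of 2.7.

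**The case against.** The strongest reply is that covariates are normally settled in a statistical analysis plan, which is not shown, and that section 2.8 offers its tests as appropriate to the data without excluding adjustment. This stands in part: a separate plan may already name the covariates. But the protocol is not silent. It lists its methods, and t-tests and rank-sum tests as named use no covariate.

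It can also be said that the gain is small and rests on an assumed R², that the SD of 5 may already contain this variance, and that 54 per arm is the low end. Section 2.1.5 keeps dropouts in the full analysis set and asks for as many of their assessments as possible, so the number with outcomes lies between 54 and 68 per arm. All of this stands.

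A reader might be tempted to infer more than the documents support:
- **That early postoperative recovery drives the outcome.** No section links time since surgery to LARS change. The 4.1-point fall under sham is not attributed to recovery; a sham response, or regression to the mean after selection on a score of at least 21, would fit equally well. No reason is given for the one-month wait, which literally times confirmation of the diagnosis and not enrolment.
- **That the open-ended window biases the comparison, or that chance imbalance is a separate uncorrected error.** Randomisation keeps the estimate unbiased in expectation, and the unadjusted standard error already covers chance imbalance.
- **That 136 is too small.** It reproduces without any adjustment.
- **That adjustment costs only one degree of freedom.** Baseline score and centre also have to be fitted.

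**Conclusion.** The point holds as a low-cost improvement in method. Section 2.8 names unadjusted tests for a change-score outcome although baseline score, the stratification factor and a date needed for eligibility could all be used. The planned comparison is valid; it is less precise than it could be.

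The case for baseline LARS score and centre rests on the design itself, since one defines the outcome and the other the randomisation. The case for time since surgery is weaker: it is plausible, but its strength is unknown from the documents. On an assumed 2–10% of the remaining variance, power at 54 per arm goes from about 79% to 80–83%. If it explains nothing, the loss is about 0.4 of a percentage point. These figures assume SD 5, a difference of 2.7 and two-sided α = 0.05. With all 68 per arm observed, unadjusted power is already about 88%.

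**What to change.** State in section 2.8 that the primary analysis is an ANCOVA, or a mixed model, of week-8 LARS score with treatment, baseline LARS score and centre, and that time since resection or stoma closure is a further pre-specified baseline covariate. Define one origin for that time, for example whichever of the two events is later, state the form in which it enters the model (such as its logarithm), and give the date a field on the CRF.

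Eligibility, stratification and the total of 136 need no change.

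The cost is a sentence or two in section 2.8 and one CRF field. In the model it is one degree of freedom for baseline score, one for time, and the number of centres minus one for centre (the number of centres is not given). This should be settled before any unblinded data are seen; if a statistical analysis plan already exists, the two documents should say the same.

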2.1.4 Exclusion criteria

① History of other types of colorectal cancer surgery or resection of other intestinal segments, including Hartmann’s procedure, abdominopelvic resection, transanal endoscopic microsurgical resection, or sigmoid colon resection;

② History of other pelvic surgeries for non-neoplastic conditions;

③ Preoperative fecal incontinence;

④ History of mental disorders, alcohol abuse, or drug abuse;

⑤ Diagnosis of inflammatory bowel disease or irritable bowel syndrome;

⑥ Received acupuncture treatment within the past one months;

⑦ Presence of implantable medical devices, such as a cardiac pacemaker;

⑧ Participated in another clinical study;

2.1.5 Criteria for Withdrawal (Dropout)

① Participants who have signed informed consent, passed eligibility screening, and entered the randomized trial but subsequently discontinue the intervention or fail to complete the observation period as outlined in the protocol will be classified as dropout cases;

② In the event of a participant’s withdrawal, investigators should make every effort to contact the individual, document the reasons for withdrawal, and complete as many assessments as possible. All relevant trial records for dropout participants must be properly retained for archiving and for inclusion in full analysis set (FAS) statistical processing. Participants who withdraw will not be replaced.

2.1.6 Suspension criteria

A participant will be withdrawn from the study under any of the following conditions:

① The occurrence of serious adverse events (SAEs), severe complications, or the need for reoperation, where the investigator determines that continued participation is not in the patient’s best interest;

② The development of other medical conditions that interfere with study assessments or make completion of acupuncture treatment infeasible, as judged by the investigator; such participants will be considered treatment failures;

③ Significant protocol deviations during trial implementation that compromise the evaluation of acupuncture efficacy;

④ The participant voluntarily requests to withdraw from the clinical trial during the study period by notifying the attending physician.

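### Section 2.1.6 withdraws participants from the study for undefined protocol deviations, which conflicts with the follow-up and analysis-set rules in 2.1.5 and 2.8 and can lose week-8 LARS scores selectively

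*Protocol*

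**What the plan says.** Protocol 2.1.6 opens with "A participant will be withdrawn from the study under any of the following conditions" and lists four grounds. Ground 3 is "Significant protocol deviations during trial implementation that compromise the evaluation of acupuncture efficacy". Grounds 1 and 2 name the investigator as judge; ground 3 names nobody. Ground 4 is the participant's own request, so ground 3 reaches people who have not asked to leave. Ground 2 adds that "such participants will be considered treatment failures".

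Protocol 2.1.5 classes as dropouts those who stop the intervention or do not finish observation. On withdrawal it tells investigators to "document the reasons for withdrawal, and complete as many assessments as possible", and it keeps the records "for inclusion in full analysis set (FAS) statistical processing". Dropouts are not replaced.

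Protocol 2.8 says "A modified intention-to-treat (mITT) approach will be applied", followed by "All randomized participants who meet inclusion criteria will be included in the statistical analysis". It does not mention the full analysis set, and 2.1.5 does not mention mITT.

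Protocol 2.10, item 2, issues a randomisation number only once eligibility has been confirmed. Protocol 2.3 leaves the acupuncturists unblinded and blinds patients, outcome assessors and analysts. Protocol 2.5 makes change in LARS score at week 8 the primary outcome.

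**The concern.** Three sections deal with the same participant and do not agree. Under 2.1.6 someone with a serious enough deviation leaves the study. Under 2.1.5 that person should still be assessed where possible and analysed. Under 2.8 the person is analysed if the inclusion criteria were met, in a set with another name. A site can follow 2.1.6 literally, stop collecting questionnaires, and be within the protocol.

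Ground 3 is also judged after randomisation and by its effect on the evaluation of efficacy, so removal may be related to outcome. Section 2.4 forbids additional LARS therapies during the study. A participant who is doing badly and seeks such a therapy commits a deviation that ground 3 could cover. Deviations need not be balanced either: section 2.4 sets stimulation to the highest tolerable level in the electroacupuncture arm and delivers no current in the sham arm.

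At stake is the randomised comparison on the primary outcome. An analysis plan can address missing scores, but it cannot recover scores that a conduct rule allowed sites not to collect.

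**Working it through.** **1. The sections side by side**

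| Question | 2.1.5 | 2.1.6, ground 3 | 2.8 |
| --- | --- | --- | --- |
| Does follow-up continue? | Yes, as far as possible | Withdrawn from the study; silent on further assessment | Not addressed |
| Is the person analysed? | Yes, in a full analysis set that is not defined | Not addressed | Yes, if inclusion criteria are met |
| Is adherence a condition? | No | Deviation triggers withdrawal | No |

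Nothing in the text removes participants with deviations from the analysis set. The gap is whether their week-8 score exists to be analysed, and which of two named sets is primary.

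**2. The inclusion-criteria condition in 2.8**

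The inclusion criteria in 2.1.3 are age, confirmed LARS (score at least 21, at least one month after resection or stoma closure) and written consent. All are fixed before randomisation, and 2.10 checks eligibility before a number is issued. The condition therefore either does almost nothing or permits a few exclusions after randomisation, with no rule on who decides or whether they are blind.

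**3. The plan's own figure**

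Inputs from 2.2 and 2.8: improvements of 6.8 and 4.1 points, SD 5, 20% dropout, two-sided α = 0.05. Power is not stated; 80% is assumed.

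- Planned difference: 6.8 − 4.1 = 2.7.
- Per arm: n = 2 × (1.960 + 0.842)² × 5² / 2.7² ≈ 53.8, so 54.
- With dropout: 54 / 0.80 = 67.5, so 68 per arm and 136 in total.

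This reproduces the stated 136. Under the normal approximation, power is 88.3% with 68 per arm and 80.1% with 54. Losses up to the planned 20% are thus covered for power. They are not covered for bias.

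**4. Size of a possible bias (illustration)**

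Let a share f of one arm lose the week-8 score, and let those people improve by g points less than those kept. The mean of those kept exceeds the full-arm mean by f × g, so a complete-case difference shifts by f × g. The documents give neither f nor g.

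| f (assumed) | g (assumed) | Shift, f × g | Share of 2.7 |
| --- | --- | --- | --- |
| 5% | 3 | 0.15 | 6% |
| 10% | 6.8 | 0.68 | 25% |
| 5% | 2.7 | 0.135 | 5% |
| 20% | 5 | 1.00 | 37% |

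The first two rows are the main illustration; the last two bound a wider range of f with a narrower range of g. A gap of 6.8 is large: in an electroacupuncture arm whose kept members improve by 6.8, it means that those lost do not improve at all.

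**5. Direction**

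Poor responders lost from electroacupuncture enlarge the difference. Poor responders lost from sham shrink it. Equal f × g in both arms cancels in expectation.

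**The case against.** The strongest reply is that 2.1.5 and 2.1.6 can be read together: the participant is withdrawn, investigators still try to "complete as many assessments as possible", and the record is analysed. Anyone withdrawn under 2.1.6 fits the dropout definition in 2.1.5. This stands as a possible reading, so a lost week-8 score is a risk and not a documented fact. It does not remove the conflict, because 2.1.6 uses the language of leaving the study and never refers back to 2.1.5.

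Three stronger inferences are tempting, and the text does not support them:

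- *The analysis becomes close to per-protocol.* Section 2.8 calls it modified intention-to-treat, states the modification and sets no adherence condition. The inclusion-criteria restriction concerns facts from before randomisation.
- *The bias favours electroacupuncture.* Both arms have 20 sessions, and nothing in the protocol shows higher attrition under electroacupuncture.
- *Unblinded staff decide the removals.* Section 2.1.6 does not say who judges ground 3. Section 2.10, item 7, keeps principal investigators blinded and separates study functions. The acupuncturists do know the allocation, so influence by arm is possible but not shown.

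It is also fair to say that the size rests on assumed inputs and on a complete-case analysis that the protocol does not specify. The handling of missing data may be in a statistical analysis plan that is not shown, and its absence is not counted here. Whether follow-up continues is a matter of conduct, and that belongs in the protocol.

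**Conclusion.** The concern holds as a conflict among 2.1.5, 2.1.6 and 2.8. Ground 3 provides for withdrawal from the study on an undefined ground judged after randomisation. Followed literally, it can lose the primary outcome in participants selected by adherence or response. The full analysis set and the mITT set are not reconciled, and the treatment-failure label in ground 2 has no stated meaning for a continuous change score.

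The bias can go either way. The range of 0.15 to 0.68 points depends on loss in one arm only, on the assumed share and gap, and on a complete-case analysis. It shows that a modest selective loss could matter against a planned effect of 2.7 points; it does not estimate what will happen. The exclusion for unmet inclusion criteria is a minor part of the point and should affect few participants.

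**What to change.** Amend 2.1.5, 2.1.6 and 2.8 as follows:

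- **Ground 3.** Remove protocol deviation as a reason to leave the study. Record it as a deviation and use it only to define a per-protocol sensitivity set.
- **Follow-up.** State that stopping acupuncture does not by itself end LARS follow-up, which continues where feasible unless consent to follow-up is withdrawn.
- **Grounds 1 and 2.** Leave the clinical judgement unchanged. Reconcile both grounds with 2.1.5, and say how the treatment failures of ground 2 enter the change in LARS score.
- **Analysis set.** Use one primary set under one name in 2.1.5 and 2.8: all randomised participants, analysed as randomised. Drop the inclusion-criteria condition from the primary set.

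The cost is a short amendment and a few more self-rated questionnaires. Keeping participants who deviated or stopped early may slightly dilute the effect estimate. The planned 136 need not change on this account.

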**2.2 Sample size**

Based on previous study, we speculated that the LARS score would be decreased by 6.8 points in the electroacupuncture group and 4.1 points in the sham-electroacupuncture group, with a standard deviation of 5. Considering a 20% dropout rate, it is estimated that a total of 136 subjects will need to be recruited.

**2.3 Randomization and Blinding Procedures**

A stratified block randomization method will be employed, with stratification based on study centers. Eligible participants will be randomly assigned in a 1:1 ratio to either the electroacupuncture (EA) group or the sham acupuncture (SA) group. The randomization sequence will be generated using SAS software by an independent statistician who is not involved in any aspect of the trial. Randomization numbers will be managed and safeguarded by a designated randomization coordinator, who will not participate in the intervention, outcome assessment, or statistical analysis.

For each eligible participant enrolled, the screening personnel will obtain the corresponding randomization number by phone from the randomization coordinator. Throughout the trial, the randomization sequence will remain concealed from all other study personnel to ensure allocation concealment.

Blinding will not be applied to the acupuncturists due to the nature of the intervention. However, patients, outcome assessors, and statistical analysts will remain blinded to group allocation to minimize potential bias.

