**2.4 treatment protocol**

Participants will be randomly assigned in a 1:1 ratio to either the electroacupuncture (EA) group or the sham acupuncture (SA) group. Acupuncture interventions will be administered by licensed Traditional Chinese Medicine (TCM) acupuncturists at each study center. All practitioners are required to hold a valid TCM physician license issued by the People’s Republic of China and possess at least three years of clinical experience.

A standardized acupuncture protocol will be employed in the EA group, with two alternating sets of primary acupoints:

Set 1: Zhongliao (BL33), Ciliao (BL32), Sanyinjiao (SP6), and Taixi (KI3)

Set 2: Tianshu (ST25), Shuidao (ST28), Zusanli (ST36), and Yinlingquan (SP9)

Only one set of acupoints will be used per treatment session, with the two sets alternated throughout the intervention period. Detailed acupoint locations are provided in Table 1.

Sterile, single-use Hwato-brand acupuncture needles (0.40 mm × 30 mm or 0.25 mm × 30 mm) will be used for all procedures. Prior to needling, both the acupoint sites and the practitioner’s hands will be disinfected thoroughly with 75% alcohol. Manual needle insertion will follow the balanced reinforcing-reducing technique through bidirectional rotation for 30 seconds to elicit the “deqi” sensation. After achieving deqi:

In Set 1, electroacupuncture stimulation will be applied to bilateral BL32 and paired between SP6 and KI3.

In Set 2, stimulation will be applied to bilateral ST25 and paired between ST36.

The intensity of electrical stimulation will be adjusted to the maximum tolerable level that produces slight tremor at the needle handle. A continuous wave at 10 Hz will be used, and all needles will be retained in situ for 30 minutes.

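### Randomisation is stratified by centre but no named analysis is stated to include centre; if centres differ, the test is mildly conservative and gives up a little power

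*Protocol*

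**What the plan says.** Protocol section 2.3 makes study centre the only stratification factor: "A stratified block randomization method will be employed, with stratification based on study centers". Allocation is 1:1. Section 2.4 adds that treatment is delivered locally: "Acupuncture interventions will be administered by licensed Traditional Chinese Medicine (TCM) acupuncturists at each study center". Practitioner as well as patient mix can therefore vary by centre.

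The analysis is in section 2.8: "Between-group differences in outcomes will be analyzed using t-tests, rank-sum tests, ANOVA, or χ² tests, as appropriate". For outcomes measured repeatedly, "For repeated measures outcomes, repeated-measures ANOVA will be employed". Neither sentence mentions centre, and no other section says how centre enters an analysis. The number of centres, their sizes and the block size are not given.

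**The concern.** Blocking within centre forces near-equal arms in every centre. Differences between centres then largely cancel out of the treatment comparison, and the estimated difference varies less from trial to trial than under simple randomisation. A two-sample test does not know this. It leaves the between-centre variance in its error term and reports a standard error suited to a less precise design.

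Two things are at stake. The confidence interval and p-value would not match the way patients were allocated. Some power would also be given up in a trial whose size appears to be set at 80%, with little to spare. Section 2.8 goes beyond silence here: it names specific methods, and most of them cannot take account of the factor used in section 2.3.

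**Working it through.** **Inputs from the protocol.** Section 2.2: decreases of 6.8 and 4.1 points, so a difference of 6.8 − 4.1 = 2.7; SD 5; dropout 20%; total 136. Section 2.8: two-sided α = 0.05. Power is not stated.

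**Reproducing 136.** n per arm = 2 × (1.960 + 0.842)² × 5² / 2.7² = 53.8, rounded up to 54. Allowing for dropout, 54 / 0.8 = 67.5, rounded up to 68 per arm, or 136 in total. The same steps give 156 at 85% power and 184 at 90%, so 136 implies 80%. This is an unadjusted comparison of two means, and nothing below changes it.

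**Assumption.** Let v be the share of the variance (SD 5, so 25) that lies between centres. The protocol gives no value; I use 0, 0.05, 0.10 and 0.15, with exact balance within centres.

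**Standard error.** The unadjusted SE is 5 × √(2/54) = 0.962 whatever v is (large-sample approximation). The true standard deviation of the estimated difference is 0.962 × √(1 − v). The ratio is 1/√(1 − v).

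**Power.** With the critical value t = 1.983 on 106 degrees of freedom:
- unadjusted: Φ[(2.7 − 1.983 × 0.962) / (0.962 × √(1 − v))]
- centre in the model: Φ[2.7 / (0.962 × √(1 − v)) − 1.983]

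The unadjusted power must also rise with v, because the blocking has already made the point estimate more precise. Holding it at its v = 0 value would overstate the gain.

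| v | SE too large by | Power, unadjusted | Power, with centre | Gain (points) |
|---|---|---|---|---|
| 0 | 0% | 79.5% | 79.5% | 0 |
| 0.05 | 2.6% | 80.1% | 81.5% | about 1 |
| 0.10 | 5.4% | 80.7% | 83.5% | about 3 |
| 0.15 | 8.5% | 81.4% | 85.6% | about 4 |

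(The 79.5% at v = 0 is below 80% only because the t critical value replaces 1.960, which gives 80.1%.)

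**Simulation.** I took 108 evaluable patients, 3 or 6 equal centres and blocks of 4 (all assumed), with 6,000 runs per scenario. The table gives the range over 3 and 6 centres.

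| v | Mean unadjusted SE / true SD | Type I error, unadjusted | Power, unadjusted | Power, with centre |
|---|---|---|---|---|
| 0 | 1.00–1.01 | 0.049–0.051 | 0.80 | 0.80 |
| 0.05 | 1.02–1.03 | 0.047–0.049 | 0.80–0.81 | 0.81–0.82 |
| 0.10 | 1.03 | 0.039–0.040 | 0.81–0.82 | 0.83–0.84 |
| 0.20 | 1.07–1.08 | 0.036–0.037 | 0.83 | 0.87 |

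Type I error with centre in the model stayed at about 0.05 throughout. At the larger values of v the SE excess is smaller than the formula gives (1.03 against 1.054 at v = 0.10), as expected with few centres. The true SD of the unadjusted estimate fell from about 0.96 at v = 0 to 0.86–0.88 at v = 0.20, so the precision from stratifying is present even when the test ignores it.

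**The case against.** The strongest reply is that section 2.8 does not exclude centre. It lists ANOVA, to be used where suitable, and ANOVA or repeated-measures ANOVA can carry a centre factor. Covariate terms are often left to a statistical analysis plan, and one may exist. This stands to a point: the documents support saying that no analysis is stated to include centre, not that none will. It does not remove the concern. The t-test, rank-sum and chi-square tests are named on equal terms and cannot carry centre, so the stated method allows the primary comparison to ignore the design.

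Second, centre effects may be small. The primary outcome is a change from baseline, which removes much of any stable difference in severity between centres. Section 2.4 standardises the acupuncture, and section 2.10 requires common procedures, central training and a consistency check across centres. This also stands. A value of v near zero is plausible, and at 0 to 0.05 the SE excess is only 0 to 3%.

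Three stronger readings are tempting, and the documents do not support them:
- A reader might infer that the benefit of stratifying is lost. It is not: balance within centres and the more precise point estimate remain. What is lost is credit for that precision in the interval, the p-value and part of the power.
- A reader might infer that the standard errors are certainly too wide. That depends on a between-centre variance the protocol does not give.
- A reader might infer a threat to validity. The error is conservative and cannot raise the false-positive rate above 5%.

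**Conclusion.** The point holds in a conditional form. Sections 2.3 and 2.8 do not match: patients are randomised within centre, and no named analysis is stated to account for centre. If outcomes differ between centres, the unadjusted analysis is conservative. The estimate is unbiased and the 136 stands.

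The cost is modest: a standard error up to about 8.5% too large and up to about 4 points of power over the assumed range of 0 to 15%, and nothing if centres do not differ. These figures assume 54 evaluable per arm, a total SD of 5 that includes centre variation, and balance within centres that survives dropout. They apply to the continuous primary outcome. For the category-improvement endpoint the same reasoning gives the direction, but I have not put a number on it.

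**What to change.** In section 2.8, state that the primary week-8 comparison of LARS change and the other continuous-outcome models include study centre as a fixed effect, with a rule set in advance for pooling very small centres. State that the category-improvement endpoint is compared by a Cochran-Mantel-Haenszel test stratified by centre, or by logistic regression with centre as a term.

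This costs about one sentence. Centre is already known from randomisation, and no further patients or data are needed. The statistical price is one degree of freedom for each centre beyond the first. With 6 centres and no centre effect, simulated power was 0.795 with centre against 0.801 without, a difference of negligible size. The change should be fixed before unblinding, so that the choice between adjusted and unadjusted tests cannot depend on the results.
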